**Fig. 2 Fig2:**
[figure not shown]
Experimental design. CePeM, Centro de Pesquisa Clínica Multiusuário; LABSAU, Laboratory of Physical Activity and Health Promotion; BIOVASC, Laboratory of Clinical and Experimental Research in Vascular Biology; HUCFF, Hospital Universitário Clementino Fraga Filho

### Intervention

Patients in the intervention arm will participate in an RT program for 6 months. The exercise sessions will consist of (a) 10-min specific warm-up, consisting of one set of 20 repetitions with loads corresponding to 50% of the resistance used in the first exercise of the training session; (b) 45-min of resistance exercises for the major muscle groups of the upper and lower body (8 single and multi-joint exercises with free weights and machines, including seated rowing, leg press, bench press, leg flexion, pull down, leg extension, shoulder press, and abdominal exercises), performed with 2–3 sets of 8–12 repetitions with loads ≥ 70% of one-repetition maximum (1RM) interspersed with 2 min intervals between sets; and (c) 5-min recovery with stretch and cool-down exercises. The OMNI-res scale will be used after each set of resistance exercises to rank patients’ perceived exertion [30]. All training sessions will occur indoors (21–23 °C), three times a week on nonconsecutive days, from 7 to 10 am, and under the supervision of the research staff. The patients will be instructed on the importance of the benefits of regular RT to improve adherence to the intervention.

### Primary outcomes measures

#### Dual X-ray absorptiometry (DXA)

Body composition will be assessed using a Prodigy-GE densitometer (GE Lunar Prodigy Advance, GE Healthcare Madison, WI, USA). Appendicular skeletal muscle mass (ASM) will be calculated with the results obtained. BMD at the lumbar spine (L1–L4), femoral neck, total femur, and one-third distal radius will be expressed in absolute values (g/cm^2^) and as standard deviations (SD) from the expected BMD for the age-matched population. A *Z*-score ≤ − 2.0 SD is considered a low bone mass for age, whereas a *Z*-score above 2.0 is within the expected range for the period, according to the 2019 Official Positions of the International Society for Clinical Densitometry. All DXA measurements will be performed by the same experienced technologist [31].

#### One repetition maximum (1RM) test

The dynamic strength maximal assessed by the 1RM test will be used to determine the loads applied during the RT program. After the general warm-up of 5 min, the volunteers will perform a specific warm-up set of 8 repetitions at approximately 50% of the estimated 1RM, followed by another set of 3 repetitions at 70% of the estimated 1RM. The patients will be verbally encouraged to perform 3 to 5 attempts for each exercise with a rest interval of 5 min between them. An interval of 10 min will be allowed before the start of the test for the next exercise. The 1RM will be determined as the higher load achieved.

#### Handgrip strength test and sarcopenia cutoff points

Isometric maximal handgrip strength will be measured by hand dynamometer TSD121C Hand Dynamometer (Biopac Systems, Inc., CA, USA) with the patients seated in a chair, with elbows flexed and the forearm in supinated position (dominant arm). The patients will perform three attempts of 5 s interspersed with 2-min intervals, and the highest value will be recorded as a result.

Sarcopenia will be detected by cutoff points of low muscle strength and low muscle mass, assessed by the handgrip test and ASM measurement, respectively, defining it as probable or confirmed sarcopenia, according to current consensus [19]. Sarcopenia cutoff points for low muscle strength from Dodds et al. [32] and low muscle mass from Baumgartner et al. [33] will be applied, considering the ratio between ASM by DXA and height squared (ASM index) of 5.45 and 7.26 kg/m^2^ and a handgrip strength of 16 and 27 kg for women and men, respectively.

#### Biochemical parameters

##### Methodology for hemogram, glycemia, lipid profile, and blood total protein evaluations

Hemogram will be performed by automatically counting blood cells from whole blood samples. Plasma glucose levels will be determined by the colorimetric glucose oxidase method. Blood will also be collected to assess the serum insulin levels and lipid profile. Serum insulinemia will be evaluated by an electrochemiluminescent immunoassay (Elecsys Insulin Assay, Roche Diagnostics GmbH, Mannheim, Germany) through an automatic analyzer (Cobas e411; Roche Diagnostics, Munich, Germany), as previously described [34]. The serum levels of triglycerides (TG), total cholesterol (TC), high-density lipoprotein cholesterol (HDL-c), and total proteins will be assessed by colorimetric methods glycerol-phosphate oxidase/peroxidase, cholesterol oxidase/peroxidase, direct detergent, and biuret, respectively. All analyses will be performed using commercially available kits suitable for an A25 automatic analyzer (BioSystems, Barcelona, Spain). Low-density lipoprotein cholesterol (LDL-c) will be calculated using the Friedwald equation [35].

##### Methodology for determinations of calcium, phosphorus, and total alkaline phosphatase blood concentrations

Analysis of serum levels of calcium, phosphorus, and total proteins will be performed by colorimetric methods purple phthalein, phosphorus molybdate, and Modified Roy [36], respectively. All analyzes will be performed using commercially available kits from Latest (Lagoa Santa, Minas Gerais, Brazil) using an automatic analyzer.

##### Methodology for determination of blood levels or activity of bone metabolism biomarkers using enzyme immunoassays (ELISA)

In this study, we will determine the following: blood levels of amino-terminal propeptide of type 1 procollagen (P1NP), osteocalcin, and blood activity of bone alkaline phosphatase (BAP), which are related to bone formation. In addition, we will also assess the blood levels of the soluble ligand of nuclear factor kappa B receptor activator (sRANKL) and degradation products of C type I collagen telopeptide (CTX-1), both related to bone resorption. We will also measure parathyroid hormone (PTH) and vitamin D blood levels [37–39].

Blood levels of sRANKL will be determined by sRANKL HS ELISA technique (Biomedica Medizinprodukte GmbH, Vienna, Austria) [40]. In this assay, the soluble RANKL present in the samples binds to the recombinant human osteoprotegerin that coats the microplate wells. Then, the sRANKL already bound to osteoprotegerin is recognized by a goat polyclonal anti-sRANKL biotinylated detection antibody. Horseradish peroxidase (HRP)-conjugated streptavidin is added to wells and binds to the sRANKL biotinylated detection antibody. The solution containing the substrate of the enzyme peroxidase (hydrogen peroxide) and chromogen (tetramethylbenzidine (TMB)) is added to the microplate. At this stage, the peroxidase present in the sample wells reacts with hydrogen peroxide, and the reaction product oxidizes TMB, changing the color of the solution to blue. The intensity of the color is directly proportional to the concentration of the conjugated enzyme and, consequently, of the sRANKL.

Blood levels of vitamin D and P1NP will be evaluated by vitamin D (Calbiotech, El Cajon, CA, USA) [41] and P1NP ELISA Kit (MyBioSource, San Diego, CA, USA) [42], respectively. In brief, these assays are based on the competitive interaction between biotin-labeled vitamin D and P1NP and those unlabeled vitamin D and P1NP (present in standards or samples) which bind to antibodies specific to vitamin D and P1NP that coat the microplate wells. After incubation, the unbound vitamin D and P1NP are washed off, and then, avidin conjugated to HRP is added to each microplate well and incubated. The amount of bound HRP conjugate and color intensity developed after substrate solution addition are inversely proportional to the amount of vitamin D and PINP present in the samples.

Osteocalcin will be measured using the Osteocalcin EIA kit (DRG International, Inc., Springfield, NJ, USA) [43]. This sandwich format ELISA kit utilizes two antibodies: one immobilized on the microplate wells and a biotynilated one, which is incubated with standards and samples. After a washing cycle, a second incubation with a streptavidin-HRP conjugate is performed. After the addition of substrate solution, which contains hydrogen peroxide and TMB, the HRP activity is determined by means of the color intensity developed which is directly proportional to the amount of osteocalcin present in standards and sample wells.

The serum levels of PTH will be determined by the PTH ELISA kit (DRG International, Inc., Springfield, NJ, USA) [43]. In this assay, antibodies raised against two specific regions on the PTH molecule are present. One of them is biotinylated while the other is HRP-labeled. Both form the sandwich complex necessary for PTH detection. The biotinylated antibody present in the sandwich complex binds to streptavidin that coats the microwells. Thus, standards and samples are simultaneously incubated with biotin- and HRP-labeled antibodies in streptavidin-coated wells. After the incubation period, the microplate wells are washed to remove unspecific bindings, and the TMB-containing substrate solution is added. The color intensity developed is directly proportional to the PTH levels in the samples.

Serum crosslaps (CTX-1) (Immunodiagnostic Systems, IDS, Boldon Colliery, UK) [44] will be used to determine the serum and plasma concentrations of human CTX-1 degradation products. This sandwich ELISA assay is based on two highly specific monoclonal antibodies against the amino acid sequence of EKAHD-ß-GGR. In order to detect specifically the CTX degradation products, the two chains of EKAHD-ß-GGR should be cross-linked. The two monoclonal antibodies, one biotinylated and the other HRP-conjugated, are simultaneously incubated with standards and samples on microtiter wells pre-coated with streptavidin.

Since the complex between the cross-linked EKAHD-ß-GGR and biotin- and HRP-labeled antibodies are formed, it binds to the microplate immobilized streptavidin by means of the biotinylated antibody. After this incubation, the wells are washed and the chromogenic substrate is added, and the observed optical density is directly proportional to the levels of CTX-1 degradation products.

BAP blood activity will be evaluated using the Quidel MicroVue BAP kit (Quidel, San Diego, CA, USA). This assay consists, firstly, of the capture of BAP present in the samples by a monoclonal antibody anti-BAP. After capture, the enzymatic chromogenic substrate, p-nitrophenol phosphate, is added to each well, and the color intensity will be read spectrophotometrically, which is proportional to the BAP activity [45].

All procedures will be performed according to the instructions provided by the kits’ manufacturers, and the optical density of each of the 96-wells of the microplate will be measured using an Universal Microplate Reader (Bio Tek model ELX 800, Winooski, VT, USA).

The levels or activity of bone metabolism markers will be determined by correlating the optical density value of the samples with the optical density values of the standard curve with the aid of an adequate data analysis program (KC Junior, Bio Tek, Winooski, VT, USA).

#### High-resolution peripheral quantitative computed tomography (HR-pQCT)

Volumetric BMD and bone microarchitecture will be measured on the non-dominant distal radius and tibia using a three-dimensional HR-pQCT system (XtremeCT, Scanco Medical AG, Brüttisellen, Switzerland), as previously described [46]. The variables that will be analyzed include the following: (i) volumetric BMD for total, trabecular, and cortical regions (Tt.vBMD, Tb.vBMD, and Ct.vBMD; mg of hydroxyapatite/cm^3^); (ii) cortical thickness, calculated by dividing the cortical volume by the external bone surface (CtTh; mm); (iii) percentage of trabecular bone volume, i.e., ratio of BV to total volume (BV/TV; %); (iv) trabecular thickness (TbTh; mm); (v) trabecular number (TbN; 1/mm); (vi) trabecular separation (TbSp; mm); and (vii) SD of TbSp (TbSp 1/N SD; mm).

### Secondary outcomes measures

#### Anthropometry measurements

An electronic scale and stadiometer (Welmy™ W300A, São Paulo, SP, Brazil) will be used to measure body mass and height. Body mass index (BMI) will be calculated as the weight, in kilograms, divided by the squared height, in meters. Neck, waist, and hip circumferences will be measured by flexible measuring tape according to the standard procedures, and waist-to-height ratio will be calculated.

Presurgery weight and minimum postsurgery weight will be self-reported by patients [47]. EWL and rate of weight regain (RWR) will be calculated as follows: (i) EWL = (presurgery weight − minimum postsurgery weight)/(presurgery weight − ideal weight for BMI of 25 kg/m^2^) × 100% and (ii) RWR = (current weight − minimum weight postsurgery)/(presurgery weight − minimum weight postsurgery) × 100% [48].

#### Hemodynamic and cardiometabolic risk factors measurements

Resting blood pressure and heart rate will be assessed in the non-dominant arm by a semi-automated oscillometric device (G-TechTM BSP11, Hangzhou, Zhejiang, China) in a controlled and quiet environment after 10-min resting in a sitting position, according to the standard recommendations [49]. Cardiometabolic risk factors will be evaluated by BMI, waist circumference, blood pressure, triglycerides, HDL-c, LDL-c, total cholesterol, and fasting plasma glucose [50].

#### 36-Item Short-Form Health Survey (SF-36)

Health-related QoL will be assessed using the SF-36 [51]. This tool consists of scores varying from 0 to 100 in eight health domains (physical function, physical role, pain, general health, vitality, social functioning, emotional role, and mental health). A higher score reflects better health perception. Those who grade 50 points or less will indicate poorer health than the reference population [52].

#### Venous occlusion plethysmography and nailfold videocapillaroscopy

Vascular function (reflected by endothelial-dependent and independent vasodilation) will be evaluated by venous occlusion plethysmography (HokansonTM AI6, Bellevue, WA, USA). There will 4 stages as follows: (1) baseline forearm blood flow (FBF) 1, (2) FBF during reactive hyperemia (after 5-min forearm arterial occlusion with pressure 50 mmHg above SBP), (3) baseline FBF 2, and (4) FBF after 5 min of 0.4 mg sublingual nitroglycerin (Nitrolingual BurnsAdler Pharmaceuticals™, Charlotte, NC, USA). FBF will be measured for 2 min at each stage with 3 min intervals for each phase will be performed, except between reactive hyperemia and baseline FBF 2, which will 15 min for washout of vasodilating substances created during ischemia [53].

Microvascular function and morphology will be evaluated through nailfold videocapillaroscopy. The capillary diameters (afferent, apical, and efferent densities), functional capillary density (i.e., number of capillaries with flowing red blood cells), baseline red blood cell velocity (RBCV), maximal RBCV (after 1 min of arterial blood flow occlusion), and time to achieve RBCVmax will be measured [53].

### Sample size calculation and statistical analysis

In this study, it will be used a similar sample size previously used in a trial which provides 90% detection power between-group differences of BMD, with a significance level of 0.05 [54]. Descriptive analysis will consist of means and SD for continuous variables and percentages for categorical variables. Data normality will be tested by the Shapiro-Wilk test with the results expressed as mean ± SD or percentage, whenever appropriate. Baseline variables will be compared between the groups using either the Student *t*-test or chi-squared test. To compare dependent variables, a two-way ANOVA will be used considering group (intervention and non-exercised control groups) and time points (pre and post-intervention), followed by the Bonferroni post hoc test, in case of significant *F* ratios. An intention-to-treat analysis will be conducted, i.e., all participants, regardless of adherence to the intervention, will be included in the final analysis. No additional analyses are planned for the study. All calculations will be performed using the GraphPad™ software (version 6.0, La Jolla, CA, USA), and the significance level will be set at *P* ≤ 0.05.

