Strategies to attenuate bone frailty and muscle atrophy in post-bariatric patients are needed, and a resistance training (RT) program can induce positive adaptations in the musculoskeletal system [20, 21], as well as in the stimulus of osteogenic response with preserved BMD in clinical studies [22–24]. In addition, RT contributes to preventing several cardiometabolic risk factors and is considered an independent predictor of all-cause mortality in the general population [25]. However, evidence of the benefits of RT on muscle and bone health in post-bariatric patients is limited. In these patients, additional studies with larger sample sizes, longer exercise interventions, higher volume, and progression overload exercises, and assessment of clinical parameters are necessary to assess the potential of RT on bone health and on fat-free mass integrity [26].

Thus, the present study will investigate the effects of an RT program on muscle mass and strength and on bone metabolism biomarkers, mineral density, and microarchitecture, and endothelial function of patients subjected to RYGB. We hypothesized that the RT program would lead to more remarkable improvement in the assessed outcomes than standard recommendations, as well as in the cardiovascular risk factors and health-related QoL.

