## Methods

### Study design

This is a randomized controlled trial, parallel-group, superiority trial with a 1:1 allocation ratio for two arms of treatment. This study protocol will be conducted at the Centro de Pesquisa Clínica Multiusuário (CePeM), Laboratory of Physical Activity and Health Promotion (LABSAU), Laboratory of Clinical and Experimental Research in Vascular Biology (BIOVASC) from the State University of Rio de Janeiro (UERJ), and at the Hospital Universitário Clementino Fraga Filho (HUCFF) from Federal University of Rio de Janeiro (UFRJ) (RJ, Brazil). Patients who were subjected to a RYGB will be recruited at our outpatients’ care unit.

Recruitment, pre-participation screening, allocation, intervention, and data collection will occur between October 2022 and December 2023. We plan that the study will be concluded, and the results will be available for analysis in December 2024. The present study protocol complies with the SPIRIT 2013 recommendations (Standard Protocol Items: Recommendations for International Trials) [27] (see Additional file 1). Figure 1 shows the schedule of enrollment, interventions, and assessments.

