### Randomization and experimental design

Sixty post-bariatric patients will be randomized through a random code generator software (www.randomization.com) at a ratio of 1:1 into two groups: (a) intervention group—that will perform a supervised RT program for 6 months—or (b) non-exercised control group—that will receive the standard clinical follow-up and shall not change their physical activity behavior. All patients will be followed by a multidisciplinary team (compose of endocrinologists, nutritionists, and physical educators) with expertise in post-bariatric patients, following the clinical practice guidelines [29]. Once the study is completed, for ethical reasons, the exercised control group will be invited to carry out the same RT program. Usual clinical care will be maintained for all patients following completion of the trial at our outpatients’ care unit.

The participants will visit our lab four times for data collection before and after 6 months post-intervention, with at least 24- to 48-h intervals between visits, as shown in Fig. 2. All assessments will be held in the morning between 7 and 11:00 am, in a quiet temperature-controlled environment (21–23 °C). The participants will be instructed to fast for 8 h for blood sample collections and vascular measures (at visit 2). The primary outcomes will be muscle mass and strength, bone metabolism biomarkers, BMD, and bone microarchitecture. The secondary outcomes will be anthropometry, hemodynamic measurement, metabolic/cardiovascular risk factors, health-related QoL, and endothelial function.

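### The group-by-time ANOVA names no term as the test of the treatment effect, does not confine post hoc tests to the interaction, and never adjusts for baseline

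*Protocol article*

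**What the plan says.** The section *Sample size calculation and statistical analysis* of the protocol article sets one method for all dependent variables: "a two-way ANOVA will be used considering group (intervention and non-exercised control groups) and time points (pre and post-intervention"). Follow-up testing is "followed by the Bonferroni post hoc test, in case of significant *F* ratios". Which F ratio (group, time or interaction) opens that step is not said, nor whether the comparisons are between arms or within them. The section then closes the list: "No additional analyses are planned for the study".

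Baseline values appear in two roles. They are one level of the time factor, and they are tested between arms: "Baseline variables will be compared between the groups using either the Student *t*-test or chi-squared test". They are not a covariate in any model.

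The aim is comparative. *Study design* describes a "parallel-group, superiority trial with a 1:1 allocation ratio for two arms of treatment", and the hypothesis in *Background* is that "the RT program would lead to more remarkable improvement in the assessed outcomes than standard recommendations".

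**The concern.** A group-by-time ANOVA gives three F ratios, and only one answers the trial's question. The time F asks whether patients changed on average, whatever their arm. The group F averages the pre and post values, so it mixes a baseline difference that randomisation makes null with half of any treatment effect. Only the interaction asks whether the arms changed differently.

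If a significant time F is enough to proceed to post hoc testing, and those tests compare pre with post inside each arm, the trial can find a significant change with training and none in the control arm although the arms do not differ. That pattern is not a test of superiority, but nothing in the section excludes it as the basis of a claim. A common drift is plausible here: patients are enrolled at least 12 months after surgery, and *Background* describes bone and muscle loss after the procedure.

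The second matter is precision. Every patient has a baseline measurement, and the comparison of change uses it less efficiently than an adjusted comparison does.

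**Working it through.** **Inputs from the protocol article.** Sixty patients randomised 1:1, so 30 per arm (*Randomization and experimental design*); one pre and one post assessment; significance level 0.05, taken as two-sided. The article gives no pre-post correlation r, time trend, SD or effect size. These are assumed below and shown over a range.

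**The plan's own figure.** The stated 90% power for between-group BMD differences is taken from an earlier trial and cannot be reproduced without an effect size and SD. Solved backwards, 30 per arm gives 90% power for a standardised difference of (1.960 + 1.282) × √(2/30) = 0.84. The article has no figure to set against this.

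**Step 1: the valid term.** With two time points, the repeated-measures interaction F is the square of the t statistic comparing mean change between arms. In simulation with no treatment effect it was significant in about 5% of trials at every drift and every r tried.

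**Step 2: how often post hoc testing opens.** With no treatment effect and no drift, at least one of three F ratios is significant in about 1 − 0.95³ = 14% of trials. Let δ be a drift common to both arms, in SDs of the change score. The time test has non-centrality δ√60; at δ = 0.4 this is 3.10 against a critical value of 2.00 (58 df), and the time F is significant in 86% of trials.

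**Step 3: training arm significant, control arm not.** Each within-arm test has non-centrality δ√30; at δ = 0.4 this is 2.19. With Bonferroni for two comparisons the critical value is 2.30, so each arm is significant with probability 0.46. Treating the arms as independent, training-only significance is about 0.46 × 0.54 = 25%. Simulation with the pooled error term and the opening step included gives 24%. Over the range of δ (no treatment effect, 30 per arm):

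| Common drift, SD of change | Training arm only significant | Interaction significant |
|---|---|---|
| 0 | 2% | 5% |
| 0.1 | 4% | 5% |
| 0.2 | 9–10% | 5% |
| 0.3 | 18% | 5% |
| 0.4 | 24% | 5% |
| 0.5 | 21% | 5% |
| 0.7 | 6% | 5% |
| 0.9 | about 0.5% | 5% |

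The rate falls again at large drift because both arms become significant: at δ = 0.9 each arm is significant with probability 0.995, and 0.995 × 0.005 = 0.5%.

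A separate simulation expressed drift in SDs of the outcome. The SD of change is √(2(1 − r)) outcome SDs, so a drift of 0.3 outcome SD is 0.30, 0.39 and 0.67 SD of change at r = 0.5, 0.7 and 0.9. It gave training-only rates of 18%, 24% and 8%, in line with the table. By symmetry the control-only pattern is equally frequent, so if both arms lose bone or muscle, an apparent protective effect (loss significant in controls only) arises at the same rate.

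**Step 4: precision.** With outcome variance σ² and n per arm, the difference in mean change has variance 4σ²(1 − r)/n. The baseline-adjusted difference has, in large samples, 2σ²(1 − r²)/n. The ratio is (1 + r)/2.

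| Assumed r | Adjusted / change variance | Reduction |
|---|---|---|
| 0.5 | 0.75 | 25% |
| 0.8 | 0.90 | 10% |
| 0.9 | 0.95 | 5% |
| 0.95 | 0.975 | 2.5% |

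In simulation with 30 per arm and an assumed effect of 0.5 SD, power was 59% (adjusted) against 48% (interaction) at r = 0.5, 76% against 69% at r = 0.7, and 99% for both at r = 0.9.

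**The case against.** The strongest reply is that the test the trial needs is already in the planned model. The hypothesis is about greater improvement, the group-by-time term tests exactly that, and comparing change is unbiased under randomisation. This stands: the fault is that the term is not named and inference is not limited to it.

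A second reply is that the section speaks of significant F ratios without saying that any one of them suffices, and never says that the Bonferroni comparisons are within arms. This also stands. If the interaction alone opened post hoc testing, training-only significance would occur in at most about 2.4% of trials. If the comparison were between arms at 6 months, simulated false positives were 2–3%. The 24% belongs to one permitted reading and to drift near its least favourable value. It is not a forecast of what the investigators will report.

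A third reply is that baseline adjustment is a matter of efficiency, and that BMD, the only outcome with a power statement, may have a high r and so gain little. That is fair for BMD. The gain may be larger for less stable outcomes, possibly the biomarkers or SF-36.

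Three stronger readings are tempting, and the documents do not support them:

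- **Pre and post values will be analysed as independent observations.** The word repeated is absent, but time is listed as a factor and the same participants are assessed before and after. A condensed article may leave the error term to a fuller plan, so no loss of power should be charged on this account.
- **The baseline is thrown away.** It is kept as a level of the time factor; it is only not used as a covariate.
- **The plan contains no valid between-group test.** The repeated-measures interaction is one.

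**Conclusion.** The point holds as a failure to fix the inference. The article settles the model and the trigger for follow-up tests and rules out other analyses, yet leaves open which result counts as evidence that training works. So this is more than a detail left to an analysis plan.

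The cost of the open trigger depends on a drift that the documents do not give. Training-only significance runs from under 1% to about 24% over 0 to 0.9 SD of change, assuming 30 per arm, no treatment effect, a time or interaction F as trigger and Bonferroni for two within-arm comparisons. The interaction stays at 5% throughout. The precision forgone is a further 2.5% to 25% of variance for r from 0.95 down to 0.5. It is secondary for BMD if r is high there, and may matter more for other outcomes.

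Because the same paragraph governs every primary outcome, it should be settled before any data are analysed.

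**What to change.** For each continuous outcome, state that the treatment effect is the between-group difference at 6 months adjusted for the baseline value (ANCOVA, or an equivalent mixed model), reported with its 95% CI, and that this is the only test of effect. If the ANOVA is kept, the minimum is to call it repeated-measures and name the group-by-time interaction as the only test of effect.

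In either case, delete post hoc tests triggered by the group or time F and present within-arm changes as descriptive summaries.

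The cost is a few sentences of analysis wording and software that fits the chosen model, so the named package should be checked for this. No extra patients, visits or measurements are needed.
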